### *3.1.2 Analysis of secondary outcomes*

The analysis of the secondary outcomes, addressing research objectives # 5 and 6 will be similar to those done for the primary outcome. Binary outcomes will be analysed using random effects logistic regression rather than linear regression. For objectives related to self-reported behaviours, on set of these behaviours will be analysed using survival analysis.

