Objective # 5 will also be tested for exploratory outcomes (listed below). For these behavioural outcomes the trial does not have enough power to detect anything except extremely large differences between the intervention and comparison arms as being statistically significant due to the low prevalence of these behaviours at baseline. However, we perceive that it is important to gather information on these behavioural measures and to measure and report the results by trial arm.

a) Incidence of self- reported suicide behaviour during 8 months

b) Incidence of self-reported tobacco use (smoking and chewing) during 8 months

c) Incidence of self-reported alcohol use during 8 months

d) Incidence of self-reported other substance use during 8 months

e) Incidence of self-reported initiation of sex during 8 months

f) Incidence of self-reported forced sexual encounters during 8 months

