## 1.4 Data collection

The data were collected at two points; baseline and end-line assessment at 8 month from baseline.

The baseline assessment was completed in July 2015 and the end-line assessment in March/April 2016.

Inclusion criteria

- All the students enrolled and studying in class IX
- Present in the school on the day of assessment

Exclusion criteria

- None

Following data is collected from consented participants: (through contact information form)

Complete name (will not be part of the questionnaire and linked directly with the outcome assessment questionnaire)

Complete address and contact details, if available (will not be reported)

- Class, section, and roll number
- Age (in years)
- Gender
- Caste
- Marital status
- Father’s education
- Mother’s education
- Father’s occupation
- Mother’s occupation
- Baseline measures of the primary, secondary and exploratory outcomes (listed below)

Outcome Measures

The primary outcome measure is overall school climate. The secondary outcome measures are attitudes towards gender equity, knowledge of and attitude towards reproductive and sexual health, experience of bullying, violence, and depression. In addition, the following exploratory^^[[1]](#footnote-2)^^ outcome measures will also be assessed: tobacco, alcohol and other substance use, sexual behaviour, and suicide attempts. The outcome assessment measures are summarised in Table 1.

Table 1: SEHER Trial outcome assessment measures

| Outcome Indicator | Instrument | Description |
| --- | --- | --- |
| Primary Outcome | | |
| School climate | Beyond Blue School Climate Questionnaire (BBSCQ) | 28 items questionnaire; minimum and maximum score range between 0 and 28 with higher scores indicating a more favourable experience of School Climate |
| Secondary Outcome | | |
| Experience of bullying | Illinois Bullying Scale | 4 items questionnaire; score ranges between 0 and 12 with higher scores indicate experience of severe bullying; recall period: last 30 days |
| Violence (perpetration and victimisation) | Global School-based student Health Survey (GSHS) | 4 items; 2 items each on perpetration and experience of physical violence; recall period: last 8 months (since the class IX started) |
| Attitude towards gender equity | Gender Equitable Men Survey | 10 items questionnaire; minimum and maximum score range between 0 and 10 with higher scores indicating more positive attitude towards gender equity |

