| Knowledge of and attitude towards RSH | Questionnaire on knowledge and attitude of towards RSH | 8 items questionnaire; minimum and maximum score range between 0 and 8 with higher scores indicating better knowledge of and attitude towards RSH |
| Depression | Patient Health Questionnaire-9 | 9 items; minimum and maximum scores range between 0 and 27 with higher scores indicating severe depression; recall period: last 2 weeks |
| Exploratory Outcome | | |
| Substance use | GSHS | 14, items measure use of tobacco (chewing and smoking), alcohol and other substances in last 8 months (since the class IX started) and last 30 days, frequency of use in last 30 days |
| Sexual behaviour | GSHS | 4 items measure sexual behaviour, and experience of forced sex in last 8 months (since the class IX started) |
| Suicide attempts | GSHS | One item measures suicide attempt in last 8 months (since the class IX started) |

Process indicators

The coverage of each component, the quality of intervention implementation (fidelity), and the extent to which stakeholders engaged with it will be examined. Coverage indicators are collected through monthly reporting forms and quality indicators are assessed through ratings of specific components, such as the wall magazine and peer group meetings by respective supervisors, and the observations made by the intervention team during field visits. The stakeholder engagement will be examined through students’ reporting of self-coverage of intervention at the follow-up assessment.

Whole school level activities

- Number of awareness meetings held with students against planned per month
- Number of awareness meetings held with teachers against planned per month
- Number of wall magazines produced against planned per month
- Types of topics covered through wall magazine
- Number of questions addressed against questions received per month through speak-out box
- Types of questions received through speak-out box per month
- Reasons for not addressing certain issues
- Type of competitions organised against planned per month
- Number of students participated in each competition
- Number of School Health Promotion Committee meetings held against planned
- Number of health policies generated and implemented in the school

Group school level activities

- Number of peer groups formed per school
- Number of peer group meetings conducted against planned per month
- Number and types of issues addressed in peer group meetings

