### *3.1.1 Analysis of primary outcome*

The estimation of the SMD of the total score on the BBSCQ at 8 months between i) the TSM and comparison arm; ii) SM and comparison arm, and iii) the SM and TSM arm will address research objective #1, 2, and 3 respectively, see Section 1.1:

Data will be analysed at individual-level using an intention-to-treat (ITT) analysis, using a linear mixed effects model with outcome of the BBSCQ total score at 8 months with intervention arm as a covariate, and adjusting for the school-level BBSCQ score at baseline. A random effect will be included to account for clustering at school level [2-3].

Sensitivity analyses for participants who have completed both baseline and follow-up assessment (cohort analyses): Independent ANCOVA-type analysis for sample of students who have completed both base and end-line assessment, using a linear mixed effects model with outcome of BBSCQ total score at 8 months with intervention arm as a covariate and adjusting for the BBSCQ total score at baseline and school. A random effect will be included to account for clustering at school level.

The data of the students who have completed base and end-line assessment will be matched through the unique identity number given to each participant.

For gender segregated sample for the participants who have completed end-line assessment: Independent ANCOVA-type analysis for sample of only boys and girls, using a linear mixed effects model with outcome of BBSCQ total score at 8 months with intervention arm as a covariate and adjusting for the school-level BBSCQ score at baseline. A random effect will be included to account for clustering at school level.

Model assumptions of normally distributed data, and the missing at random assumption, will be tested (see section 3.1.3) and if necessary, the outcome analyses will be adapted as appropriate.

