## 3.2 Exploratory analyses

The following are all follow-on analysis.

The models may be extended to include possible predictors of outcome including intervention coverage and students’ self-reporting of coverage.

Inclusion of TSM and SM characteristics in models will be considered.

Any analysis of sub-scales or domains will also be reported as exploratory.

Analysis procedure described in 3.1.1 will be followed for the exploratory outcomes (listed in 1.10.

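### Behavioural outcomes are assigned both to survival analysis and to a linear SMD model, although the SAP lists no onset times and already names a logistic model for binary outcomes

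*SAP*

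**What the plan says.** Three places in the SAP bear on how the self-reported behaviours are analysed.

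- Section 3.1.2, which covers objectives 5 and 6, first gives a general rule: "Binary outcomes will be analysed using random effects logistic regression rather than linear regression". The next sentence reads: "For objectives related to self-reported behaviours, on set of these behaviours will be analysed using survival analysis".
- Section 3.2 gives another route: "Analysis procedure described in 3.1.1 will be followed for the exploratory outcomes". Section 3.1.1 describes an individual-level analysis "using a linear mixed effects model with outcome of the BBSCQ total score at 8 months with intervention arm as a covariate", with a school random effect, reported as an SMD.
- Section 1.1 ties the two together: "Objective # 5 will also be tested for exploratory outcomes (listed below"). The six outcomes are suicide behaviour, tobacco, alcohol, other substances, initiation of sex and forced sexual encounters. Each is defined as an incidence, for example "Incidence of self-reported alcohol use during 8 months".

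On the data, section 1.4 says: "The data were collected at two points; baseline and end-line assessment at 8 month from baseline". Table 1 describes the items by recall window. The suicide entry is typical: "One item measures suicide attempt in last 8 months (since the class IX started"). Substance use is asked over the same window and over the last 30 days, with frequency of use in the last 30 days. Table 1 mentions no date, month or age of onset. The SAP gives no time origin, event-time definition, censoring rule or survival model.

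**The concern.** An analyst cannot follow 3.1.2 and 3.2 together for the same outcome. One yields a hazard ratio or an odds ratio, the other an SMD. Neither the survival route nor the linear route fits the items as listed. Survival analysis needs event times, and two surveys with recall windows mainly say whether something happened. The linear route divides a difference in proportions by the SD of a 0/1 variable.

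The denominator is also open. The outcomes are called incidence, but the analysed set is everyone who completed the end-line survey, including students never assessed at baseline, and no at-risk set is defined.

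At stake are the effect measure and the denominator for suicide behaviour, substance use and sexual behaviour. The SAP intends to report these by arm, so the choice should not be made after the data are seen.

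**Working it through.** The plan states no figure for this point, so the check is of fit between data and model, with an illustration.

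**1. Instructions side by side**

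| Source | Applies to | Model | Effect measure |
|---|---|---|---|
| 3.1.2, general rule | binary outcomes under objectives 5 and 6 | random-effects logistic | odds ratio |
| 3.1.2, next sentence | onset of self-reported behaviours | survival, type not stated | presumably a hazard ratio |
| 3.2, pointing to 3.1.1 | exploratory outcomes | linear mixed model | SMD |

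Section 1.1 places the exploratory outcomes under objective 5, so all three rows can reach them.

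**2. What one common interval does to a survival model**

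Let pC and pT be the control and intervention risks over the interval, with every event time tied at 8 months. Then:

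- Cox model with Breslow ties gives the risk ratio, pT/pC
- complementary log-log hazard ratio = ln(1−pT)/ln(1−pC)
- logistic odds ratio = [pT/(1−pT)]/[pC/(1−pC)]
- linear model: difference = pT−pC; SMD = (pT−pC)/√[p̄(1−p̄)], where p̄ is the mean of the two risks

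The SAP says only that baseline prevalence is low, so the risks below are assumptions. The Cox, complementary log-log and logistic fits used 5,000 students per arm and ignored clustering.

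| Assumed risks | Cox, Breslow | Cox, Efron | Compl. log-log | Logistic OR | Risk difference | SMD |
|---|---|---|---|---|---|---|
| 2% vs 1.4% | 0.700 | 0.698 | 0.698 | 0.696 | −0.006 | −0.046 |
| 18% vs 12% | 0.667 | 0.645 | 0.644 | 0.621 | −0.060 | −0.168 |

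Worked for the first row: 0.014/0.020 = 0.700; (0.014/0.986)/(0.020/0.980) = 0.696; −0.006/√(0.017×0.983) = −0.046.

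With no timing, the survival model reduces to a binary-outcome model. For rare outcomes the three ratio measures nearly agree; for commoner ones they spread.

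**3. Why an SMD is unsuitable here**

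The SD of a 0/1 variable is fixed by its prevalence. Holding the risk ratio at 0.700, the SMD is −0.033 for 1% vs 0.7% and −0.108 for 10% vs 7%. The same relative effect appears about three times as large only because the behaviour is commoner.

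**4. Students without baseline status**

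Section 2.1, Figure 1 gives end-line minus baseline completers by arm: 4,623 − 4,465 = 158; 5,316 − 4,525 = 791; 4,475 − 4,046 = 429. The total is 1,378. The analysed set is 4,623 + 5,316 + 4,475 = 14,414, and 1,378/14,414 = 9.6%. This is a lower bound that assumes every baseline completer was seen again; any loss raises it.

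**5. The recall anchor**

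Table 1 describes the window both as 8 months and as the time since class IX began. Recruitment of class IX students was in June 2015, the intervention began in July 2015 and end-line was March/April 2016. Eight months back from end-line is July/August 2015. Back to June 2015 or earlier is at least 9 to 10 months. The two descriptions can give different windows, and the second may include some time before the intervention.

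**The case against.** The strongest defence is that the plan already contains a workable method. Logistic regression is the rule for binary outcomes, survival analysis can be read as a specific exception for onset, and 3.2 may mean only that the general procedure of 3.1.1 carries over (intention to treat, arm comparisons, school random effect). The outcomes are exploratory, section 1.1 says that power is lacking for anything short of very large differences, and section 3.2 calls its analyses follow-on. This stands as an argument on severity. It does not remove the conflict: 3.1.1 names a linear model and an SMD, 3.2 cites 3.1.1 rather than 3.1.2, and the exception for onset has no inputs.

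A reader might go further and infer the following, which the document does not support:

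- *That the effects cannot be validly estimated.* A tied-time survival model is estimable, and a linear model on 0/1 data still gives a risk difference. The logistic model in 3.1.2 can be used directly.
- *That no onset times were collected.* Table 1 lists none, but the questionnaire is not shown. For substance use, the 30-day and 8-month windows give coarse timing, and not every item is yes/no.
- *That pre-intervention behaviour is counted as incident.* The recall wording is ambiguous and does not prove it.
- *That every behaviour should be restricted to matched, baseline-negative students.* Suicide behaviour and forced sexual encounters can recur. For these, the restriction would change the question and discard valid data.

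**Conclusion.** The point holds at moderate severity. Sections 3.1.2 and 3.2 assign the same exploratory outcomes to different models, and neither the survival nor the linear SMD route suits recall-window items from two surveys. The practical effect is on which measure and denominator are reported. Among ratio measures the choice hardly matters for rare events (0.696 to 0.700 at assumed risks of 2% and 1.4%) and matters more for common ones (0.621 to 0.667 at 18% and 12%). The SMD is on a different scale altogether. At least 9.6% of analysed students lack the baseline status that an incidence analysis needs.

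This rests on Table 1 being a fair summary of the items, on the assumed risks and on an illustration without clustering. No conclusion on the primary outcome depends on it.

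**What to change.** - In 3.1.2, delete the survival sentence, or state how onset time is obtained and give the time origin, censoring rule and model.
- In 3.2, change the cross-reference so that binary exploratory outcomes use the random-effects logistic model of 3.1.2, with a school random effect, reporting an odds ratio and a risk difference.
- Analyse end-line occurrence over the recall window in all end-line respondents, and call it period prevalence.
- For initiation-type outcomes (substance use, first sex), add an incidence analysis in matched students who were negative at baseline, and state which baseline item and recall period define negative. Do not apply this restriction to suicide behaviour or forced sexual encounters.
- State which recall window the items used, and note that it may include some time before the intervention.

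The cost is SAP wording and no new data; the identity-number matching is already planned in 3.1.1. The incidence analyses will have smaller denominators, and so even less power, than the end-line set.

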### *3.1.3 Statistical considerations*

*Time points*

The primary analysis will be of the 8 months outcome for total score on the BBSCQ.

*Clustering*

School (cluster) will be included as a random-effect covariate in the regression.

*Covariates*

Socio-demographic variables such as age, marital status, caste, and parents’ education and occupation will be included as covariates in the analysis model, irrespective of arm-wise balances among them at baseline.

*Adjustment for multiple outcomes and reporting p-values*

Interpretation of the intervention effect will be based on the strength of evidence of effect size and consistency of results for related outcomes.

*Missing outcome data*

Missing outcome data will be imputed using multiple imputations, implemented in Stata.

*Model assumption checks*

The models assume normally distributed outcomes; this will be checked when describing the data. Model residuals will also be plotted to check for normality and inspected for outliers. If substantial departures from normality occur, transformations will be considered. If a suitable transformation cannot be found, a non-parametric analysis will be considered.

A sensitivity analysis that assesses the effect of deviations from the missing at random assumption on the intention to treat treatment differences for the primary outcome may be considered if there are considerable amounts of missing data (6). Sensitivity analysis will be conducted comparing results with and without imputation.

## 3.2 Exploratory analyses

The following are all follow-on analysis.

The models may be extended to include possible predictors of outcome including intervention coverage and students’ self-reporting of coverage.

Inclusion of TSM and SM characteristics in models will be considered.

Any analysis of sub-scales or domains will also be reported as exploratory.

Analysis procedure described in 3.1.1 will be followed for the exploratory outcomes (listed in 1.10.

## 3.3 Cost-effectiveness analysis

Cost data specific to the interventions (TSM and SM) will be collected during the study period, i.e. activity based costing approach from a program perspective will be used. The program costs will include costs related to hiring, training, additional salary costs, costs of continuous supervision activities, cost of materials both for training and for continuous intervention (leaflets, posters, etc.). All costs related to research activities will be excluded from the cost estimation—this will be done in consultation with the study team (for example, proportion of study team used for research activities, travel costs related to collection of research data etc. will be excluded). Total cost will be estimated separately for the two arms of the intervention using unit costs, total number of months or total number of units that has been utilised by the program.

Cost estimates will be presented in terms of various process outcomes used in the study. Incremental cost-effectiveness (CE) ratio, however, will be estimated for the primary outcome and estimated as the additional cost per unit change in mean school climate score in the intervention arms compared to the control arm. One way sensitivity analyses will be done to understand the effect of changes in cost and intervention parameters on the CE ratio.

